### Participant randomization and group allocation

Prior to group randomization, a researcher blinded to the future group allocation will classify participants into quartiles based on their peak VO_2_ values. Subsequently, participants from each quartile will be randomly assigned with a 1:1 allocation ratio to 1) supervised group: canoeing and physical activity recommendations (*n* = 18), or 2) unsupervised group: physical activity recommendations (*n* = 18). Following randomization, participants in both groups will be invited to a meeting at the School of Physical Education and Sport at the University of Sao Paulo, where the researcher and the physician will communicate the importance of an active lifestyle and the benefits of physical activity for people living with cancer. In addition, participants will be introduced to the physical activity recommendations booklet (based on WHO guidelines) produced by ICESP. The researcher and physician will outline the goal of achieving physical activity guidelines (i.e., 150 min of moderate-to-vigorous physical activity/exercise per week). Participants will be advised that recommendations can be achieved through separate bouts of activity, such as 50 min per day on three non-consecutive days each week, or 30 min 5 days a week. Following, the physician, who will be blinded to the allocation, will leave the room and the researcher will inform each participant which intervention group they have been allocated to. For participants in the supervised group (canoeing and physical activity recommendations), canoeing training schedules are explained, whereas for those participants allocated in the unsupervised group, best days and times for telephone calls will be arranged so the researcher can remotely investigate whether this group is reaching physical activity recommendations.

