### Statistical analysis

#### Power calculation and sample size

Sample size calculations were performed based on the predicted maximum oxygen consumption (VO_2_—ml/kg min) of patients with breast cancer [95] using G-Power Software (Version 3.1.9.2). Sample size was carried out a priori, assuming a power (1 − *β* error) of .90 and assuming *α* error of .05. The calculation was based on an F test with analysis of variance by repeated measures and between- and within-group effects. To eliminate possible sample size bias, the Hedges *g* calculation was used. The effect size used in the calculation was based on the work of Courneya et al. [95] considering the maximum oxygen consumption (VO_2_—ml/kg min) of patients with breast cancer. A pre- to post-test correlation value of 0.50 was assumed. Power calculations indicated a sample size of *n* = 15 participants per group were required to achieve a power = .90 and *α* error = .05. To account for participant drop-out during the intervention, the sample size was increased by 20% to *n* = 18 participants per group. Therefore, we aim to recruit a total sample of *n* = 36 participants to the study.

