## Trial status

Recruitment began in June 2018. Initially, we would expect to conclude participants’ recruitment by July 2021. However, because of the current pandemic, recruitment should be delayed. This is version 3 of the protocol. Version 1 was submitted to the Research Ethics Committee of the USP School of Physical Education and Sports on November 2017; Version 2 included the ICESP as a co-participant institution and changed the age interval inclusion criteria from 45–75 to 35–75 years. Changes in version 3 were the exclusion of pain as an outcome (and the questionnaire to assess it), removal of obesity from the exclusion criteria, and the ones after the pilot study described in the “Discussion”.

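### Baseline peak VO2 stratifies the randomisation but is a covariate only if a baseline t-test shows a difference; which women define the quartiles is also left open

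*Protocol article*

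**What the plan says.** In Participant randomization and group allocation, before allocation, "a researcher blinded to the future group allocation will classify participants into quartiles based on their peak VO_2_ values". The next sentence reads "Subsequently, participants from each quartile will be randomly assigned with a 1:1 allocation ratio to" a supervised and an unsupervised arm, each of 18. No cut-points, reference distribution or recruitment batches are given, and nothing is said about a quartile with an odd number of women.

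In Power calculation and sample size, "we aim to recruit a total sample of *n* = 36 participants to the study", with an assumed pre-post correlation of 0.50.

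In Trial status, "Recruitment began in June 2018"; completion was expected by July 2021 and has since been delayed by the pandemic. The Discussion says that recruitment to the main trial is under way and reports barriers already seen among women in the intervention, some of which affect attendance at the supervised sessions.

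In Data analysis, the model for every outcome, including aerobic capacity, is a linear mixed model with fixed effects for group and time and a random effect for participant. Baseline differences are tested with independent t-tests. An ANCOVA with the baseline value as covariate is used only where the groups differ at baseline.

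**The concern.** There are two linked questions. The first is whether the strata are defined. Quartiles of the whole sample are known only when the last woman has been tested, yet women are allocated and treated well before then. The cut-points must therefore come from somewhere else, and the article does not say where. A reader cannot reconstruct a woman's stratum, or tell how an odd place in a quartile is filled.

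The second matters more: whether the analysis uses the variable on which the design balances. Baseline peak VO2 is both the stratifier and the baseline value of the primary outcome. The plan makes it a covariate only after a significance test whose null hypothesis is true by randomisation and which stratification makes still less likely to reject. At stake are precision in a trial of 36 women and a primary model that is fixed before the data are seen.

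**Working it through.** **Sample size as stated.** 15 per group × 1.20 = 18; 2 × 18 = 36. This agrees with the article.

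**Allocation within quartiles.** If quartiles are taken over the whole sample, 36 / 4 = 9 women each. Nine cannot be halved, so the closest split is 5:4. Over four quartiles there are 2^4 = 16 patterns of 5:4 or 4:5:
- 18:18 in C(4,2) = 6 patterns (for example 5 + 5 + 4 + 4 = 18)
- 19:17, either way, in 8 patterns
- 20:16, either way, in 2 patterns

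If each odd place is settled by an independent fair coin, these have probabilities 6/16 = 37.5%, 8/16 = 50% and 2/16 = 12.5%. If the odd places are balanced across quartiles, 18:18 is certain.

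**Cost of the worst split.** The standard error ratio for 20:16 against 18:18 is √(1/20 + 1/16) / √(2/18) = √0.1125 / √0.1111 = 1.006, an increase of 0.6%.

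**Can whole-sample quartiles be used?** June 2018 to July 2021 is 37 months. Eligibility requires treatment to have ended between 6 months and 3 years earlier. A woman tested at the start and held until the end would be at least 6 + 37 = 43 months from treatment, beyond the 36-month limit. The Discussion also shows women already in the intervention. Whole-sample quartiles are therefore not what is being used, which leaves fixed cut-points, running quartiles or batches.

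**How far these readings differ.** In a simulation of 36 values, running quartiles (from the fourth woman on) disagreed with final-sample quartiles for about 19% of women. Batch quartiles disagreed for about 39% (batches of 6), 32% (9), 25% (12) and 19% (18). Normal values and these batch sizes are assumptions; neither is in the article. The figures show that the readings give different strata, not that any of them is biased.

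**Cost of leaving baseline out as a covariate.** Let σ² be the variance of peak VO2, taken as equal before and after, and ρ the pre-post correlation. With complete pre and post data, the group-by-time contrast in a random-intercept model is a comparison of mean changes. The section lists group and time without naming their interaction; I take this contrast to be the one intended.
- Change comparison: 2σ²(1 − ρ) = 2 × 0.50 × σ² = 1.00σ²
- Baseline as covariate: σ²(1 − ρ²) = (1 − 0.25)σ² = 0.75σ²
- Ratio: (1 − ρ²) / [2(1 − ρ)] = (1 + ρ)/2 = 0.75 at ρ = 0.50

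The standard error falls by a factor √0.75 = 0.866, about 13%. Equivalently, 36 women analysed with the covariate give roughly the precision of 36 / 0.75 = 48 analysed by change. The covariate costs one residual degree of freedom (34 to 33 with 36 women).

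**Range over ρ (assumed values).** The ratio (1 + ρ)/2 is 0.65 at ρ = 0.3, 0.85 at 0.7 and 0.90 at 0.8. The gain shrinks as ρ rises, but the ratio stays below 1 for any ρ below 1.

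**How often the trigger would fire.** The level of the baseline test is not stated. At 5%, it would fire in about 5% of trials under unstratified randomisation, and less often when allocation is balanced on the tested variable. In nearly all realisations the primary analysis would thus be the one without the covariate.

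**The case against.** The strongest reply on allocation is that nothing is broken. A 1:1 ratio is a target or a probability and does not promise equal counts in every stratum. The wording fits batches: several women are classified together, and both groups are then invited to a meeting after randomisation. Assignment that is random within a stratum is unbiased even if the stratum depends on who else was tested, and the person classifying is blinded to future allocation. List generation and cut-points are also details that a condensed article may leave to the full protocol. All of this stands, and it reduces the allocation part to a request for clarification.

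A reader might infer from nine women per quartile that 18:18 cannot be reached, or that the rule cannot be carried out. Neither follows: 5 + 5 + 4 + 4 = 18, and batch quartiles satisfy the text. A reader might also infer that odd places are filled by hand and so open to influence in an open-label trial. The article says only that assignment is random and describes no such discretion.

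On the analysis, it can be said that the mixed model does not ignore baseline, because the pre-intervention value is one of its two responses. That is true, but it enters as a subtraction with slope fixed at one, which is the change comparison costed above. Nor is this an omitted detail: the section states both the model and the condition for adjustment.

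**Conclusion.** The concern holds in a limited form. The definition of the strata is ambiguous given the trial's own recruitment timeline, with negligible effect on power (at most 0.6% on the standard error) and no demonstrated bias. The fuller protocol may resolve it.

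The substantive fault is that the analysis adjusts for the stratifying variable only after a significance test at baseline. This makes the primary model depend on the data, and under stratification it will usually select the less precise one. At the protocol's correlation of 0.50 the loss is residual variance of 1.00 against 0.75. That figure assumes equal variances at the two times, complete data and the group-by-time contrast as the treatment effect. A higher true correlation would make the loss smaller.

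**What to change.** 1. **Primary analysis.** Analyse post-intervention peak VO2 with group and continuous baseline peak VO2 as covariate, in all circumstances. Delete the baseline t-test as a trigger. With one post value per woman, no participant random effect is needed in this model.
2. **Women still to be randomised.** State the reference set for the strata, either fixed peak VO2 cut-points or named recruitment waves. Use a list generated in advance that also settles odd places. If waves are used, include wave as a factor in the model.
3. **Women already randomised.** State how their strata were formed.

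The cost is small: a few sentences of amendment and one list. Baseline peak VO2 is already collected. The covariate uses one degree of freedom, and a wave factor uses one more for each wave after the first. If the stratification rule changes part-way, the trial will contain two allocation schemes and the report should say so; unconditional adjustment for continuous baseline applies equally to both.

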#### Unsupervised group—physical activity recommendations

Participants will receive physical activity recommendations booklet (based on WHO guidelines) produced by ICESP. The booklet suggests different types of physical activity and exercise, such as aerobic, strength, and flexibility, outlines their benefits, and precautions participants should adopt while exercising. The booklet recommends exercise as part of a lifestyle behavioral change. Participants will be free to perform daily life activities and physical activity at home, at gyms or outdoors, with the aim of increasing overall physical activity including leisure time physical activity via structured exercise. A member of the research team will make telephone calls to the participants, which are scheduled to be done every 2 weeks, totalizing eight phone calls. In these calls, the researcher will apply a standardized follow-up questionnaire to monitor physical activity adherence.

### Assessments

The experimental procedures described below will be performed at baseline (Pre) and after 16 weeks of the intervention (Post), keeping an interval of 3 or 4 days after the last canoeing training session. An exception will be the evaluation of physical activity engagement (time, frequency, and intensity), which will also be monitored at 8 weeks (mid-way point of the intervention). The assessment protocol will be divided into two visits and all procedures will take place at the School of Physical Education and Sport of the University of Sao Paulo (Fig. 3). Participants will be advised to avoid performing physical activities and alcohol ingestion in the 24 h prior to the visits, to refrain from tobacco use and stimulant beverages (coffee, tea) for at least 6 h, and to take their medication as recommended by their physicians. In the first visit, the participants will arrive at 7 am, following an 8-h fasting period and undertake the procedures in the following order: 1) blood sampling; 2) anthropometry and lymphedema measurement; 3) eat a snack consisting of an apple, 150 g of salted crackers, and 200 ml of juice; and 4) cardiorespiratory fitness test. The second visit will take place at least 2 days later to allow the participant to fully recover from the fitness test. For the second visit, the participants will arrive at 7 am and undertake the following evaluation: 1) questionnaires assessing quality of life in cancer survivors, health status, fatigue, body image, and physical activity motivation; and 2) physical functioning tests.

**Fig. 3 Fig3:**
[figure not shown]
Schematic overview of the main trial data collection days; lines indicate timing of blood sampling, anthropometric measurement collection, cardiorespiratory test, questionnaires, and physical functioning analysis, over two visits

#### Blood sampling

Blood samples will be collected by puncture of a forearm peripheral vein by an experienced physician ([name]). If the participant had undergone the removal of axillary lymph nodes, the blood will be taken from the unaffected arm. Blood samples will be collected into two 4-ml BD Vacutainer® tubes coated with dipotassium ethylenediaminetetraacetic acid (K_2_EDTA) and one 5 ml BD Vacutainer® SST® tube (with silica clot activator, polymer gel, silicon-coated interior). The gel tube will be centrifuged at 2100*g* for 10 min at 4 °C to isolate the plasma and together with the K_2_EDTA tubes will be sent to the Clinical Hospital Central Laboratory (School of Medicine, University of Sao Paulo) for standard biochemical and immunological analyses. The laboratory analysis of the blood samples will include the following: complete blood and platelet count assessed using an automated analyzer followed by microscope revision; glycated hemoglobin assessed by high-performance liquid chromatography (HPLC); total cholesterol, high-density lipoprotein (HDL), non-HDL and low-density lipoprotein (LDL) cholesterol assessed using enzymatic colorimetric cholesterol oxidase phenol 4-aminoantipyrine peroxidase Isotope Dilution - Mass Spectrometry (CHOD/PAP ID-MS) assays; triglycerides assessed using enzymatic colorimetric Glycerol Phosphate Oxidase Peroxidase Amidopyrine (GPO-PAP) assay; and glucose assessed using ultraviolet (UV) enzymatic method with hexoquinase. The remaining plasma from the chemistry analysis will be stored at − 80 °C for future molecular analysis within the research objectives. An additional 25 ml of whole blood will be collected into sodium heparin BD Vacutainer® tubes and peripheral blood mononuclear cells (PBMCs) will be isolated using density gradient centrifugation using standard methods. Cells in freezing medium [70% Roswell Park Memorial Institute (RPMI) media, 20% fetal bovine serum (FBS), 10% dimethylsulphoxide (DMSO)] will be cryopreserved at − 1 °C/min using a Nalgene “[name]” container in a − 80 °C freezer and after 24–48 h will be moved to long-term storage in liquid nitrogen at − 196 °C. For immune function assays, cells will be thawed in batches, rested overnight, and examined using enzyme-linked immunospot (ELISPOT) assays. Briefly, the magnitude of interferon gamma (IFN-γ) production by T cells will be assessed in response to a variety of stimuli, including antigens from common viruses such as *Cytomegalovirus*, *Epstein Barr Virus*, *Varicella Zoster Virus*, and tumor-associated antigens pre- and post-intervention.

#### Anthropometry and lymphedema measurement

Body mass will be assessed using digital scales, and height measurements performed using a wall-mounted stadiometer, with the participant standing upright and barefoot. Body mass index (BMI) will be calculated by the measures of weight (W, kg) and height (H, m) using the equation BMI = W / H^2^. Waist circumference will be measured using a measuring tape placed around the smallest abdominal diameter. Body composition will be estimated by skinfold thickness from triceps, suprailiac, and medial thigh using an adipometer. The following protocol will be employed for conversion of body density [74]:

• % Fat (Siri’s equation) = [(4.95 / DENS) − 4.50] × 100.

• DENS = 1.099421 − 0.0009929 (X2) + 0.0000023 (X2) 2 − 0.0001392 (X3)

where X2 = sum of the skinfolds: triceps, suprailiac, and thigh; and X3 = participant’s age, in years.

Lymphedema status will be assessed by measuring the bicipital circumference. Participants will adopt the orthostatic position, with arms on the anatomical position, extended along the body. A measuring tape will be placed around the midpoint of the arm.

#### Cardiorespiratory fitness test evaluation

The laboratory temperature will be maintained between 20 °C and 22 °C. The test will be conducted on a treadmill (Inbrasport®, RS, Brazil) at least 60 min after participants have consumed the standard snack (as described previously). The test will begin with a 5-min walking at 2.0 mph to analyze walking economy. Afterwards, treadmill speed will be increased by 0.5 mph each minute until the participant achieves a maximal comfortable speed (3.0 mph, 3.4 mph, or 4.0 mph) previously defined in an adaptation test. Then, the treadmill grade will be increased by 2% each minute (Table 1) until the participants can no longer continue. Electrocardiogram will be continuously monitored (EMG System do Brazil, EMG, 030110/00B, Sao Paulo, Brazil) throughout the test and auscultatory blood pressure will be measured using a mercury column sphygmomanometer (Uniteq) at the end of the 5 min walking period and every 2 min during the progressive test. Oxygen consumption (VO_2_) will be measured with breath-by-breath sampling using a metabolic cart (CPX Ultima, Medical Graphics Corporation® CPET system, St. Paul, MN) with data analyzed by 30 s averages. Anaerobic threshold and respiratory compensation point will be determined in accordance with Skinner and McLellan’s criteria [75] by two researchers, with a third researcher consulted to solve discrepancies. Peak heart rate and peak VO_2_ will be recorded at each participant’s exhaustion.

**Table 1 Tab1:** Progressive exercise test protocol

	Target speed 3.0 mph		Target speed 3.4 mph		Target speed 4.0 mph	
Time	Speed	Grade	Speed	Grade	Speed	Grade
5 min	2.0 mph	0%	2.0 mph	0%	2.0 mph	0%
6 min	2.5 mph	0%	2.5 mph	0%	2.5 mph	0%
7 min	3.0 mph	0%	3.0 mph	0%	3.0 mph	0%
8 min	3.0 mph	2%	3.4 mph	0%	3.5 mph	0%
9 min	3.0 mph	4%	3.4 mph	2%	4.0 mph	0%
10 min	3.0 mph	6%	3.4 mph	4%	4.0 mph	2%
11 min	3.0 mph	8%	3.4 mph	6%	4.0 mph	4%
12 min	3.0 mph	10%	3.4 mph	8%	4.0 mph	6%
13 min	3.0 mph	12%	3.4 mph	10%	4.0 mph	8%
14 min	3.0 mph	14%	3.4 mph	12%	4.0 mph	10%

#### Questionnaires (pre- and post-intervention)

The questionnaires will be administered to participants by a trained researcher. To guide participants in completing the questionnaire, the researcher will explain each questionnaire and read each item aloud, encouraging participants to ask any question they may have. The following questionnaires will be administered:
i.European Organization for Research and Treatment for Cancer Quality of Life Questionnaire - Core 30 (EORTC QLQ-C30) will be used to assess a broader dimension of quality of life in cancer survivors [76]. This validated instrument is composed of three scales that examine global health, functional aspects and patient’s symptoms. It comprises 28 questions about difficulties of daily life and symptoms with scales from 1 (no difficulty/distress/symptom) to 4 (a lot of difficulty/distress/symptom), and two questions about general health and quality of life with scales from 1 (terrible quality) to 7 (great quality). The Brazilian version has been previously validated among people living with cancer [77].ii.36-Item Short-Form Health Survey (SF-36) will be used to evaluate health status [78]. It comprises eleven questions (five of which are multi-item) that evaluate health status including physical and social functioning, physical and emotional role, mental health, bodily pain, general health perceptions, and vitality. The Brazilian version of SF-36 was already applied to women with a history of breast cancer [79].iii.Piper Fatigue Scale-Revised (R-PFS) will be used as a subjective fatigue assessment method. Its psychometric properties have been validated in female survivors of breast cancer [80]. The Brazilian version contains 22 items on three dimensions (behavioral, affective, and sensorial–psychological) and provides an overall of fatigue score on a scale from 0 (the best status evaluation) to 10 (the worst status evaluation). This instrument has been validated for oncological use in Brazilian populations [81], particularly for breast cancer survivors [82].iv.Body Image Scale [83] will be used to assess body image. Its higher scores indicate greater body appreciation and it addresses six domains of body image: vulnerability, body stigma, limitations, body concerns, transparency, and arm concerns. The Brazilian version presents 44 statements for which the participant must decide how they apply to her, on a scale varying from 1 (Strongly disagree/Never/Almost Never) to 5 (Strongly Agree/Always/Almost Always). It has also been demonstrated to be reliable and valid [84].v.Inventory of Motivation to the Regular Practice of Physical Activity (IMPRAF-54, Brazilian acronym) will be used to assess physical activity motivation. The short version of this form contains 54 items for which the participant must decide how they reflect her motivation to engage on physical activity, using a scale varying from 1 (this motivates me very little) to 5 (this motivates me a lot). All affirmations start with “I engage in physical activity to...” followed by sentences that reflect six dimensions (nine items for each), such as control of stress (e.g., decrease irritation), health (e.g., acquire health), sociability (e.g., meet friends), competitiveness (e.g., be champion in sport), esthetic (e.g., accomplish a beautiful body), and pleasure (e.g., achieve my ideals) [85]. The raw score obtained in each dimension will be related to a percentile according to participant’s gender and age, which will provide the participants’ motivational profile.
